### Outcome measure

#### Patient-reported cognitive symptoms and signs

The Swedish Quality of Recovery cognitive version (SwQoR-Cog) is a self-assessment questionnaire designed to measure postoperative symptoms. The SwQoR-Cog has been developed from the original SwQoR, which measures general postoperative recovery.^23^ In the cognitive version, the number of items has been reduced, and additional items focusing on patient-reported cognitive symptoms and signs have been included. This refinement in targeting cognitive recovery is based on the previous research,^24^,^26^ clinical experience and our ongoing research in the field of neurocognitive recovery.^27^

The SwQoR-Cog consists of 14 statements regarding symptoms and discomfort. Of these, 10 address cognitive symptoms (eg, fatigue, difficulties in sleeping, reading/calculating and concentrating), while 4 pertain to general postoperative recovery. The symptoms are rated on an 11-point numerical scale, ranging from 0 (‘not at all’) to 10 (‘all the time’).

#### Neurocognitive function

A digital neurocognitive test battery (Mindmore-P) will be used to assess neurocognitive function, specifically measuring verbal episodic memory and executive functions, including visuospatial skills and selective attention (table 1). This digital test battery is self-instructive and accessible through an online platform. It is designed to be comparable to the traditional analogue International Study Group of Postoperative Cognitive Dysfunction test battery, and participants have reported a high level of usability.^28^ Preliminary results indicate that the digital test battery is feasible for use in clinical settings with older adults who have undergone major abdominal surgery (manuscript submitted). Before undergoing neurocognitive tests, the patient will evaluate their vision and hearing and rate their level of restfulness and stress using a five-point scale.

**Table 1 T1:** Included test in Mindmore-P

Test	Cognitive domain and function	Description
CERAD	Verbal episodic memory	Used to assess verbal learning skills, immediate recognition and delayed recognition. The participant is presented with ten words and then asked to repeat the words at different timepoints. At one point, the participant will be presented with a larger list of words and asked to select the correct words.
TMT A and B	Executive, visuospatial and processing speed	Measures mental and motor speed, and mental flexibility. This test requires the use of an external computer mouse for the most accurate result. The participant will be presented with letters and digits and asked to connect them in a specific order as fast as possible.
SCW	Executive, selective attention, cognitive flexibility and inhibitory control	Assesses for inhibitory control by presenting words written in different colours and asking for either naming the correct colour or naming the colour of a printed incongruent colour word. The test is time-sensitive and requires both speed and accuracy.
SDPT	Executive, visuospatial, processing speed, concentration and verbal learning	The test relies on psychomotor speed and the ability to decipher symbols. The participant is presented with symbols that represent digits as a code and then asked to click on the correct digit as many times as possible.

CERAD, consortium to establish a registry for Alzheimer’s disease; SCW, stroop colour-word test; SDPT, symbol digits processing test; TMT, trail making test (A and B).

#### Delirium

Delirium screening will be conducted using the nursing delirium scale (Nu-DESC).^29^ This scale evaluates five areas to assess the presence and severity of symptoms in patients. It uses a 3-point grading scale, where a total score of 2 or higher indicates the presence of delirium. The Nu-DESC has been validated for use with older adults in a Swedish context.^30^

#### Depression

The patient health questionnaire-9 (PHQ-9) will be used to assess depressive symptoms.^31^ This questionnaire consists of nine statements to which respondents should respond on a four-point scale. A score of 0 indicates ‘not at all’, while a score of 3 means ‘almost every day’. Respondents should consider their experiences over the past 2 weeks when answering. The PHQ-9 is a validated tool for detecting and monitoring depression.^32^

#### Frailty

The clinical frailty scale (CFS)^33^ is a validated and reliable assessment tool used for evaluating a person’s frailty. It consists of nine levels ranging from (1) very vital to (9) terminally ill. This objective assessment is conducted by trained professionals based on the individual’s habitual status prior to illness. The CFS has been validated in a Swedish context.^34^

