### Aim

The purpose of this study is to investigate the factors that influence neurocognitive function and patient-reported cognitive symptoms among patients aged 65 and older following cardiac surgery, and explore the impact on the overall postoperative recovery. Additionally, the study aims to describe the perspectives of close relatives on the recovery process. The following scientific questions will be addressed in the study.

What is the incidence of dNCR/p-NCD and the occurrence of patient-reported cognitive symptoms in older adults up to 6 months after cardiac surgery?Is there a correlation between preoperative cognitive status and dNCR/p-NCD, and if so, which cognitive function (executive function, attention and memory) is most affected?Is there a correlation between POD and dNCR/p-NCD, and if so, which cognitive function is most affected?Which factors (eg, age, educational level, duration of surgery, perceived self-efficacy, frailty and mental health and depression) affect the risk of suffering from postoperative cognitive decline?Is dNCR/p-NCD associated with increased symptom burden, impaired functional level, fatigue, frailty, deteriorated quality of life and an increased number of unplanned contacts with healthcare services?How do older adults with persistent cognitive symptom burden experience their postoperative recovery and return to daily life?How do close relatives to older adults with persistent cognitive symptom burden perceive the patient’s postoperative cognitive function and recovery, and how does this affect the relative’s own life?

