### Procedure

#### Preoperative data collection

Before surgery, the patient’s baseline data will be collected approximately 14 days in advance, following their informed written consent to participate in the study. We will measure patient-reported cognitive symptoms, self-efficacy, frailty (if it has not been routinely recorded at the hospital site), fatigue, health-related quality of life and collect demographic data. This data collection can take place digitally, at the hospital or through home visits. The process of collecting data will be thoroughly documented.

All questionnaires will be distributed using the Research Electronic Data Capture (REDCap) system. If participants prefer, the data can also be collected using paper-and-pen questionnaires or through phone assessments. Neurocognitive function will be evaluated using the Mindmore-P tool on a digital platform. Each test begins with an introduction, followed by a practice trial and then the actual test trial, which takes approximately 15–20 min to complete. Although Mindmore-P is self-instructive, a trained test leader (such as a research nurse or researcher) will be available by phone or digital platform for distance assessments, or in person at the hospital, to provide support and answer any questions that may arise. Close relatives of the participants will be asked, after providing their consent, to provide demographic information and respond to questionnaires about the patient’s cognitive function and caregiver burden prior to surgery. Table 2 outlines the outcome measures and the time points for assessment.

**Table 2 T2:** Outcome measurements and timepoint for assessment

Outcomes	Instrument	Timepoint of measurement					
		Preop	Postop day 1–7	At discharge	1 month	3 months	6 months
Participant (patient)							
Cognitive symptoms	SwQoR-Cog	X		Every seventh day → → → → → →→→→			X
Neurocognitive function	Mindmore-P	X			X	X	X
Delirium	Nu-DESC		X				
Frailty	CFS	X					X
Fatigue	FSMC	X					X
Self-efficacy	S-GSE	X			X	X	X
Depression	PHQ-9	X			X	X	X
Health-related quality of life	RAND-36	X					X
Functional level	WHODAS 2.0	X			X	X	X
Experience of postop recovery	Interview						X
Unplanned hospital visits	Study specific						X
Demographical data	Study specific	X					
Surgical and postop data	Patient record			X			
Participant (close relative)							
Cognitive assessment for others	CFQ-f	X			X	X	X
Assessment of perceived burden	ZBI-12	X			X	X	X
Experience of postop recovery	Interview						X

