#### Postoperative data collection and follow-up

After surgery, participating patients will be monitored for postoperative delirium from postoperative day 1 to postoperative day 7, or until they are discharged from the hospital. Following this period, they will be asked to evaluate their cognitive symptoms weekly for up to 3 months after surgery. The questionnaire will be distributed digitally using REDCap (table 2).

At both 1-month and 3-month post-surgery, we will assess neurocognitive function (using the Mindmore-P), self-efficacy, depression and functional capacity. At the 6-month mark (the endpoint of the study), we will also evaluate frailty, fatigue and health-related quality of life. Perioperative data will be collected from the patient’s medical records. Close relatives of the patients will complete the same questionnaires (focused on the cognitive assessment of the relative and caregiver burden) at 1-month, 3-month and 6-month postsurgery. Each follow-up session is expected to take approximately 40–50 min for the patients and about 10 min for the close relatives (table 2).

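### The single rating rule given for the Clinical Frailty Scale does not clearly fit its repeat at 6 months, and the stated analysis does not separate pre-existing frailty from postoperative change

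*Protocol article*

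**What the plan says.** Under Outcome measure, Frailty, the protocol article describes the scale: "It consists of nine levels ranging from (1) very vital to (9) terminally ill". It says that trained staff make the assessment "based on the individual’s habitual status prior to illness". No other reference period is given for the CFS, and the illness is not identified.

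The preoperative section lists "frailty (if it has not been routinely recorded at the hospital site" among the baseline measures, so a routine hospital rating may serve as baseline. Table 2 ("Outcome measurements and timepoint for assessment") marks the CFS at two points, preoperatively and at 6 months. The follow-up section confirms the repeat: "At the 6-month mark (the endpoint of the study), we will also evaluate frailty, fatigue and health-related quality of life".

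Frailty has two roles in the Aim. The fourth research question names it as a possible risk factor for cognitive decline. The fifth asks whether dNCR/p-NCD is "associated with increased symptom burden, impaired functional level, fatigue, frailty, deteriorated quality of life" and more unplanned healthcare contacts.

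Data analysis and statistics names three quantitative approaches that bear on this:

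- parametric and non-parametric tests for group differences in outcomes and demographic characteristics;
- logistic regression with neurocognitive performance as the dependent variable;
- mixed effect models, in a sentence about longitudinal data and clustering of patient-reported cognitive symptoms.

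**The concern.** A rating anchored to the time before illness suits a preoperative risk factor. It suits a 6-month outcome only if the anchor moves with the visit, and the article does not say that it does. If the anchor stays fixed, the 6-month score is a second reading of baseline.

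A second difficulty arises even if the anchor moves. The plan itself expects that patients who are frail beforehand may decline cognitively more often. A plain comparison of 6-month CFS between patients with and without dNCR/p-NCD would then differ for that reason alone. At stake is whether the frailty part of the fifth question can be answered as something separate from the fourth.

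**Working it through.** The article gives no figure to reproduce. The check sets the statements side by side and writes out what each reading implies.

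**Notation.** Let F be frailty before the cardiac illness, H0 the habitual state around the preoperative visit, and H6 the habitual state at 6 months. Let D = H6 − H0 be the postoperative change. Let R0 and R6 be the recorded scores, with rating errors e0 and e6.

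**Reading A: the illness is the cardiac disease leading to surgery.**
- R0 = F + e0 and R6 = F + e6.
- R6 − R0 = e6 − e0. D does not appear, so any difference is rater or recall variation.
- Group difference at 6 months (dNCR/p-NCD minus none), apart from error = difference in F. This is the fourth question again.

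**Reading B: the illness is any acute illness present when the rating is made.**
- R0 = H0 + e0 and R6 = H6 + e6 = H0 + D + e6.
- R6 − R0 = D + (e6 − e0). Change can be captured.
- Group difference at 6 months, apart from error = difference in H0 + difference in D. The first term is non-zero whenever preoperative frailty is related to cognitive decline, as the fourth question allows. An unadjusted comparison cannot tell the two terms apart.

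**Which reading does the article support?** The Frailty section does not settle it. Reading A is natural in a cardiac surgery cohort. Reading B fits better with repeating the scale at all, and with listing it at 6 months beside fatigue and quality of life. Other instruments are given a clear window: PHQ-9 covers the past 2 weeks, WHODAS 2.0 refers to current health, and the CFQ-f window was shortened from 6 months to 1 month to suit recovery. No comparable statement is made for the 6-month CFS.

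**Does the stated analysis isolate D?** In the logistic regression, neurocognitive performance is the dependent variable, so frailty can enter only as an explanatory variable. The mixed-model sentence names patient-reported cognitive symptoms. For frailty as an outcome, that leaves the between-group tests, which carry no baseline term.

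**The case against.** The strongest reply is that the Frailty section describes the instrument in general terms, as the neighbouring sections do for theirs, and sets no rule by visit. Repeating the scale at 6 months makes sense only if status at that time is rated, so trained raters would probably do so. This has force. A reader might infer from the wording that the 6-month CFS cannot show any postoperative change and that the expected change is zero. The article does not support that as a flat statement, because it holds only under Reading A and the illness is undefined. A reader might also suppose that a given share of the change, such as half, would be lost if raters followed different rules. Nothing in the article says how raters would divide, so no such share can be given.

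It can also be said that the fifth question asks only about association. That is correct, and the article does not claim that cognitive decline causes frailty. The difficulty is that the association, as measured, may be the one already covered by the fourth question.

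Finally, rater instructions and covariate lists often sit in a fuller protocol or analysis plan. Their absence here is not the point. The point is that the one rule stated does not clearly fit one of its two stated uses, and that the methods stated do not provide a baseline-adjusted analysis of frailty. The mixed-model sentence could be read more broadly as covering all longitudinal data. Even so, it would not settle the reference period.

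The limited scope of the matter is conceded. WHODAS 2.0 also follows functional level preoperatively and at 1, 3 and 6 months.

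**Conclusion.** The point holds in a conditional form. The stated CFS rule and the 6-month use need to be reconciled. Under Reading A the 6-month score carries no information on postoperative change; under Reading B it does, but the article leaves the choice open. Under either reading, an unadjusted 6-month comparison includes whatever difference in frailty existed before surgery.

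The first part rests on what the undefined illness is taken to mean. The second rests on preoperative frailty being related to cognitive decline, which the fourth question treats as possible and the Introduction lists among identified risk factors.

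The effect is confined to the frailty item of the fifth question. The incidence of dNCR/p-NCD, the sample size of 220 and the use of preoperative frailty as a risk factor are untouched. The size of any attenuation or mixing cannot be quantified, because the article gives no CFS distribution, no expected change and no rater agreement.

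**What to change.** 1. In the Frailty section, state the reference period for each rating. Say which illness the preoperative rule refers to, and that the 6-month CFS rates the patient's habitual status at that visit. Put the same wording in the rater instructions, so that the Frailty section agrees with the Aim, Table 2 and the follow-up section.

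2. For the frailty item of the fifth question, analyse 6-month CFS with preoperative CFS as a covariate, using a model suited to a nine-level ordered score. A single baseline rating carries error, so adjustment need not remove all of the earlier difference, but it directs the question at change.

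3. Recruitment began in November 2024 and March 2025. Adding 6 months, and ignoring the roughly 14 days before surgery, ratings fall due from about May and September 2025. For any made before the clarification, record which reference period the rater used, where this is known.

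The cost is one or two sentences and a covariate that is already planned. No new visits, instruments or participants are needed.

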#### Self-efficacy

The general perceived self-efficacy scale^35^ is a ten-item questionnaire that allows respondents to answer on a four-point scale. It measures the respondents’ belief in their ability to face challenges and resolve problems. The instrument has undergone validity testing in Sweden.^36^

#### Health-related quality of life

The RAND-36 will be used to assess health-related quality of life. This instrument consists of 36 questions divided into 8 domains: physical function, limitations due to physical health, limitations due to emotional problems, energy and fatigue, emotional well-being, social functioning, pain and general health. In addition to the total score, two summary scores will be calculated: the physical component summary and the mental component summary. These summaries reflect the overall physical and mental health status. The RAND-36 has been translated into Swedish and has been reliability tested.^37^

#### Functional capacity

The WHO disability assessment schedule 2.0^38^ measures an individual’s level of daily activity. It consists of 12 questions regarding the difficulty of completing everyday activities in relation to the respondent’s current health. Respondents can answer on a 5-point scale, with scores ranging from 0 to 4. Higher scores indicate increased disability.^39^

#### Fatigue

The fatigue scale for motor and cognitive functions measures fatigue in relation to cognitive and physical functioning. This questionnaire consists of 20 statements regarding how fatigue impacts a person’s everyday life. Respondents can rate each statement on a five-point scale, with higher scores indicating more severe fatigue. The assessment results will categorise fatigue as mild, moderate or severe.^40^

#### Cognitive assessment of close relatives

The cognitive failures questionnaire for others (CFQ-f) is designed for close relatives to assess cognitive difficulties observed in their loved ones during daily activities.^41^ It consists of eight questions, each rated on a five-point scale ranging from ‘never’ to ‘always’. This questionnaire has been translated into Swedish by our research group using back-translation techniques. It has also been adapted for the Swedish context to ensure that the wording is appropriate for the Swedish language and culture. The timeline has been modified to focus on the past month rather than the last 6 months, as in the original questionnaire, to better align with the recovery process.

#### Caregiver burden

The short form of the Zarit Burden Interview (ZBI-12) will be used by close relatives to evaluate their perceived burden.^42^ It comprises 12 questions, with responses rated on a 5-point scale from ‘never’ to ‘almost always’. The ZBI-12 short form has been tested for validity and reliability in the Swedish context.^43^

#### Demographic and perioperative data

This will include sociodemographic and perioperative data, such as civil status, educational level, hearing and visual impairments, comorbidities, American Society of Anesthesiologists (ASA) classification, duration of surgery and anaesthesia, other clinical characteristics and postoperative complications. Any unplanned health visits will be documented at the endpoint.

#### Experiences of postoperative cognitive recovery

To gain a better understanding of the recovery process for older adults following cardiac surgery, specifically regarding cognitive recovery, qualitative interviews will be conducted with patients and their close relatives. The semi-structured interview guide for patients will include questions, such as: ‘can you describe what a typical day has been like for you since the surgery?’ and ‘have you experienced any patient-reported cognitive symptoms or difficulties since the surgery, and what do they entail?’ The interview guide for close relatives will feature questions like: ‘can you share your experiences since the surgery and how it has impacted you and (the name of the person who underwent the surgery)?’ and ‘how has the recovery process affected your daily life?’

### Procedure

#### Preoperative data collection

Before surgery, the patient’s baseline data will be collected approximately 14 days in advance, following their informed written consent to participate in the study. We will measure patient-reported cognitive symptoms, self-efficacy, frailty (if it has not been routinely recorded at the hospital site), fatigue, health-related quality of life and collect demographic data. This data collection can take place digitally, at the hospital or through home visits. The process of collecting data will be thoroughly documented.

All questionnaires will be distributed using the Research Electronic Data Capture (REDCap) system. If participants prefer, the data can also be collected using paper-and-pen questionnaires or through phone assessments. Neurocognitive function will be evaluated using the Mindmore-P tool on a digital platform. Each test begins with an introduction, followed by a practice trial and then the actual test trial, which takes approximately 15–20 min to complete. Although Mindmore-P is self-instructive, a trained test leader (such as a research nurse or researcher) will be available by phone or digital platform for distance assessments, or in person at the hospital, to provide support and answer any questions that may arise. Close relatives of the participants will be asked, after providing their consent, to provide demographic information and respond to questionnaires about the patient’s cognitive function and caregiver burden prior to surgery. Table 2 outlines the outcome measures and the time points for assessment.

**Table 2 T2:** Outcome measurements and timepoint for assessment

Outcomes	Instrument	Timepoint of measurement					
		Preop	Postop day 1–7	At discharge	1 month	3 months	6 months
Participant (patient)							
Cognitive symptoms	SwQoR-Cog	X		Every seventh day → → → → → →→→→			X
Neurocognitive function	Mindmore-P	X			X	X	X
Delirium	Nu-DESC		X				
Frailty	CFS	X					X
Fatigue	FSMC	X					X
Self-efficacy	S-GSE	X			X	X	X
Depression	PHQ-9	X			X	X	X
Health-related quality of life	RAND-36	X					X
Functional level	WHODAS 2.0	X			X	X	X
Experience of postop recovery	Interview						X
Unplanned hospital visits	Study specific						X
Demographical data	Study specific	X					
Surgical and postop data	Patient record			X			
Participant (close relative)							
Cognitive assessment for others	CFQ-f	X			X	X	X
Assessment of perceived burden	ZBI-12	X			X	X	X
Experience of postop recovery	Interview						X

CFQ-f, cognitive failures questionnaire for others; CFS, clinical frailty scale; FSMC, fatigue scale for motor and cognitive functions; GSE, general perceived self-efficacy scale; Nu-DESC, nursing delirium scale; PHQ, patient health questionnaire; SwQoR-Cog, Swedish quality of recovery cognitive version; WHODAS, WHO disability assessment schedule; ZBI, Zarit burden interview.

